### Adverse Events and Dropouts

Adverse events will be mentioned and recorded throughout the trial for participant safety. Information about adverse events, including the date and participant’s experience, will be summarized in tables. Information about participants who discontinued the study will be recorded. Furthermore, the reasons for dropout, such as COVID-19 symptoms, loss to follow-up, and sickness, will be reported.

### Study Arms and Content

There will be 3 different study arms. As intervention groups (A and B), the first and second arms will receive pelvic or lumbar supports for 4 weeks. As the control group (C), the third arm will only receive a patient education leaflet containing advice on strengthening exercises, comfortable positions, and other practical information. The outcomes include pain, effort score during the ASLR test, maximum isometric hip flexion force, maximum isometric hip external rotation force, maximum isometric trunk rotation force, and joint position reproduction (JPR) of hip abduction. The study outcomes will be measured at 4 time points: baseline (T1), immediately after the intervention (T2), 4 weeks after the interventions began (at this time, the intervention period is completed) (T3), and 1 week after discontinuing the interventions (T4) to evaluate the possible lasting effects of wearing supports. The study process is outlined in Figure 1.

**Figure 1 figure1:**
[figure not shown]
The study flowchart for the randomized controlled trial.

### Intervention

This study will use 2 orthoses: pelvic (Group A) and lumbar (Group B) support (Teb Darman Co). Both orthoses are made of breathable textile material to comfort the participant. Orthoses can be worn on top of or under daytime clothes. The pelvic support will be an adjustable strap (10-15–cm width) fastened below the anterior superior iliac spine (Figure 2A). The lumbar support consists of a pelvic belt attached to the lumbar corset. Lumbar support has a 25-cm width anteriorly and extends from the xiphoid process to the pelvis. It has a 35-cm width posteriorly and extends down from the lower angle of the scapula to gluteal prominences (Figure 2B). Group C (control) will receive only a patient education leaflet containing advice on strengthening exercises, comfortable positions, and other practical information. Participants will be instructed to incorporate the regular activities into their daily routines and not use pain relief medication or other treatment during the following 5 weeks. Although we do not expect participants to experience any trial-related harm, they will be provided with a direct number to contact should they have any questions or queries and report any symptoms related to interventions or any discomfort experienced while wearing their orthoses.

**Figure 2 figure2:**
[figure not shown]
Study interventions: (A) pelvic support and (B) lumbar support.

### Outcome Measures

All tests will be carried out with a certified orthotic practitioner. Table 1 outlines the outcome measures and shows how outcome measures will be measured at different time points throughout the study.

**Table 1 table1:** The outcome measures of the study.

Measures	Baseline (T1)	Immediate effect (T2)	Fourth week (T3)	Fifth week (T4)	
Overall pain	✓	✓	✓	✓	Visual analog scale
Effort score during active straight leg raise	✓	✓	✓	✓	6-point Likert scale
Maximum isometric hip flexion force	✓	✓	✓	✓	Digital force gauge
Maximum isometric trunk rotation force	✓	✓	✓	✓	Digital force gauge
Maximum isometric hip external rotation force	✓	✓	✓	✓	Digital force gauge
Joint position reproduction of hip abduction	✓	✓	✓	✓	Kinovea software
Activity limitation	✓	✗	✓	✓	Modified Oswestry Disability Index

### Primary Outcome Measures

#### Pain

The participant will indicate the severity of pain related to the lumbopelvic region during the previous week on a 10-point VAS ranging from 0 to 10, where 0=no pain and 10=the worst imaginable pain [24]. The VAS is documented and recommended as reliable in subjects with lower back pain (SE 0.09, intraclass correlation coefficient [ICC] 0.90) [37].

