### Participants

Women with postpartum PPGP will be recruited through a simple (convenience) sampling method from the obstetric outpatient clinics of IUMS. The examiner will confirm the diagnosis with the presence of PPGP, and positive diagnostic tests include the following: ASLR, posterior pelvic pain provocation (also known as P4) test, Patric-Faber test, and Gaenslen’s test [33]. The inclusion criteria of the study are (1) primipara women who experienced natural delivery (one month before); (2) age between 18 and 45 years; (3) self-reported pregnancy-related PPGP; (4) a pain score of at least 40 out of 100 mm on the visual analog scale (VAS) [17]; and (5) a score of higher than 2 out of 5 on a 6-point Likert scale for perceived effort during the ASLR test [34]. The exclusion criteria were as follows: (1) the presence of lower back or pelvic pain before pregnancy; (2) history of any fracture in the pelvis and lower extremities; (3) history of spine, pelvis, and lower extremity surgery; (4) neurological diseases; (5) limb length discrepancy; (6) congenital anomaly in the spine, pelvis, and lower extremities; and (7) using any other conservative treatment for pain relief during the study, such as physiotherapy treatment methods. All eligible participants will provide informed consent and sign the consent form before inclusion in the trial. Participants will be free to withdraw at any time during the study.

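### The primary pain score asks about the previous week but is also collected immediately after the intervention (T2), where it cannot show an immediate effect

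*Protocol article*

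**What the plan says.** - **Pain item.** Under the heading "Primary Outcome Measures", the Pain subsection reads: "The participant will indicate the severity of pain related to the lumbopelvic region during the previous week on a 10-point VAS". The scale runs from 0 to 10. No other recall period or pain wording appears for any visit.
- **Visits.** Study Arms and Content sets the schedule as "baseline (T1), immediately after the intervention (T2), 4 weeks after the interventions began (at this time, the intervention period is completed) (T3", with T4 one week after the supports are stopped. The Abstract gives the same schedule.
- **What is measured at each visit.** In the same section, "The outcomes include pain, effort score during the ASLR test" opens the list of outcomes to which the four-visit schedule applies. Table 1 heads the second column "Immediate effect (T2") and ticks overall pain at all four visits. Its row "Activity limitation", the Oswestry index, is crossed out at T2.
- **Scale.** The Participants section sets eligibility as "a pain score of at least 40 out of 100 mm on the visual analog scale (VAS"), which is a different scale from the 0 to 10 of the Pain subsection.

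**The concern.** T2 exists to capture what the support does straight away. The other measures kept at T2 (effort during the leg raise, the three isometric forces, and joint position reproduction) are taken during a test at the visit, so they can respond at once. Pain is the exception, because it asks about a week that is nearly over before the intervention begins.

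A woman can answer at T2 in two ways. She can answer the question as put, and describe almost the same days she described at baseline. Or she can ignore the recall period and report how she feels now, which is not what she was asked at T1. The data would not show which she did. Under Assignment, Randomization, and Blinding, the assessor is not masked after allocation, so any unscripted prompt towards current pain would come from someone who knows the arm.

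At stake is one of the four assessments of a primary outcome. Pain reduction is also the first aim stated in the Introduction. A null T2 result could be read as no immediate benefit when the question could not have detected one.

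**Working it through.** **Step 1. Fix the timing of T2.** T3 is defined as the end of the 4-week wear period, so T2 cannot be the end of wear. It must fall at the start, as its Table 1 label says.

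**Step 2. Share of the recall window after the intervention.** The plan gives no figure of its own to reproduce here. The inputs are the recall period of 7 days = 168 hours (Pain subsection) and the interval *h* from application to T2. The interval is not stated, so it is taken as an assumption and shown as a range.

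Share after the intervention = *h* / 168.

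| Assumed interval *h* | Share after | Share before |
|---|---|---|
| 0 h | 0% | 100% |
| 30 min | 0.5/168 = 0.3% | 99.7% |
| 1 h | 1/168 = 0.6% | 99.4% |
| 2 h | 2/168 = 1.2% | 98.8% |
| 4 h | 4/168 = 2.4% | 97.6% |
| 24 h | 24/168 = 14.3% | 85.7% |

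For a same-session T2 (up to 4 hours), about 98 to 100% of the window precedes the intervention. Even a full day later the figure is 86%.

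**Step 3. What a literal answer can show.** Assume the answer is a time-average over the window and the intervention changes pain by a constant amount from the moment it is applied. The T2 score then carries only the share-after fraction of that change: at most 2.4% at 4 hours and 14.3% at 24 hours.

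**Step 4. Check the other visits.** At T3 the previous week is the last week of wear. At T4 it is the week after stopping. Both windows match what those visits are meant to measure, so the mismatch is confined to T2.

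**Step 5. Look for a repair elsewhere in the article.** There is no current-pain or pain-during-test score. The effort score during the leg raise rates difficulty, not pain. Data Analysis names a multivariate ANOVA with Bonferroni post hoc tests and does not exclude T2 pain.

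**The case against.** Four points can be made for the plan.

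*The damage is limited.* This stands. T3 and T4 pain are coherent, the lumbar-support-versus-control pain aim can be answered at T3, T2 is not named as the primary time point, the Oswestry index is not collected at T2, and no sample-size figure changes.

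*If women report current pain at T2, the randomised arms can still be compared at that visit.* This stands in part. If every participant answered that way, the between-arm contrast at T2 would be a fair comparison of current pain, and only the T1-to-T2 change would mix two questions. But nothing in the article ensures a uniform answer, and a protocol should not rely on participants disregarding its wording.

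*An article condenses the full protocol.* This would excuse an omission. Here the recall period and the schedule are both stated, and they do not fit together.

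*The effect on the overall analysis is not established.* This also stands. A reader might infer that a null T2 halves the overall arm effect, taking 0.44 to at most 0.22. The documents do not support that:

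- With arm effects of 0, 0, δ and at most δ at T1 to T4, the four-visit mean is at most 2δ/4 = δ/2. Without T2 it is still at most 2δ/3. T2 accounts only for the step from 2/3 to 1/2, a reduction of one quarter; the rest comes from T1.
- Averaging visits also reduces the SD. With equal between-visit correlation ρ (an assumption), the standardised effect of the four-visit mean would be 0.22/√((1+3ρ)/4): 0.28 at ρ = 0.5 and 0.24 at ρ = 0.8.
- The 0.44 in Sample Size is (64.4 − 58.2)/13.945 = 0.445, where 13.945 pools the SDs 13.93 and 13.96. These are baseline means from a previous study, so 0.44 is not a treatment effect at T3.
- Data Analysis does not say that visits are averaged. A group-by-time test, or one treating the visits as an outcome vector, would not average the T3 effect down in this way.

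**Conclusion.** The concern holds, restricted to pain at T2. As written, the previous-week score cannot show an immediate effect: about 98 to 100% of its window precedes the intervention if T2 is in the same session, and 86% does so even at 24 hours. Answered literally, it essentially repeats T1; answered as current pain, it makes the T1-to-T2 change a mixture of two questions. This rests on the single pain wording given and on an assumed interval to T2. That T2 nearly duplicates T1 also assumes that the two are close together, which the article does not state, but the conclusion that the T2 window is nearly all pre-intervention does not depend on it.

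Pain at T3 and T4 is unaffected, and no size is claimed for any dilution of an overall effect.

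The scale difference is a minor side issue. A 0 to 10 and a 100 mm scale differ by a factor of ten, which leaves a standardised effect unchanged. A reader might infer that the sample size was documented on the 100 mm scale. Its means of 58.2 and 64.4 cannot be 0 to 10 scores, but the section states no unit.

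**What to change.** Keep the previous-week pain score at T1, T3 and T4, and remove it at T2 from Table 1 and from the analysis. Then choose one of two options:

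1. Add a separate current-pain score, worded identically at T1 and T2, and use it only for the immediate effect; or
2. Collect no pain score at T2, as Table 1 already does for the disability index, and confine the immediate-effect question to the performance measures.

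The first option keeps an immediate pain comparison; the second is simpler. State one pain scale throughout, either 0 to 10 or 100 mm, so that eligibility and outcome scores are recorded alike.

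The cost is at most one extra scale line at two visits, plus edits to Table 1 and to the outcome and analysis text. The sample size does not change. The change needs to be made before data collection, because the question a participant had in mind cannot be recovered afterwards.

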#### Modified Oswestry Disability Index for Lower Back Pain

The Persian version of the Oswestry Disability Index (ODI) will quantify disability in women with postpartum PPGP [38]. This self-reported 10-item questionnaire has been introduced as a valid and reliable tool compatible with spine-related disabilities [39]. The first item evaluates the pain intensity. The other items ask about pain intensity experienced while carrying out typical daily activities, including personal care, lifting, walking, sitting, standing, sleeping, social life, traveling, and employment/homemaking. Each item scored 0-5; higher scores imply higher pain intensity and disability. The ODI has been introduced as a gold standard for lower back functional outcome tools and has good psychometric properties, which can be used in various settings [40]. The ODI shows a good construct validity, acceptable internal consistency (Cronbach α=.69-.87) [38,41,42], and high test-retest reliability (*r*=0.83-0.99) in people with lower back pain [41-43].

### Secondary Outcome Measures

#### Effort Score During ASLR

With the participant lying in supine position on the examination table, they will be instructed to keep their knee straight with their feet 20 cm apart during tests. The raising height during the ASLR test will be defined by placing a metal bar 20 cm above the examination table (target position) [44]. The perceived effort will be scored while the participant raises their leg to the target position. They will indicate their perceived difficulty in performing the test on a 6-point Likert scale ranging from 0 to 5, where 0=no problem and 5=unable to do [44]. The test-retest reliability of the ASLR test was reportedly high in women with pregnancy-related PPGP (information coefficient 0.82) [44].

#### Maximum Isometric Force

Maximum isometric muscle force measures will be obtained with a portable digital force gauge (SF-500, Akurasi, R.O.C). It will be periodically calibrated in accordance with the manufacturer’s information manual.

##### Maximum Isometric Hip Flexion Force

A digital force gauge will be attached to the metal bar and adjusted to be placed immediately above the ankle. The participant will be asked to raise their involved leg and compress the force gauge probe while their leg is still lying on the table [15]. The maximum isometric hip flexion force test correlates well with the ASLR test. The test will be repeated 3 times at a 20-second interval. The mean value will be recorded.

##### Maximum Isometric Hip External Rotation Force

The participant will undergo isometric muscle strength testing for external hip rotation using a digital force gauge and a stabilization strap. He/she will be asked to sit upright on the chair with his/her hip and knee positioned in approximately 90° flexion [45]. The stabilization strap will be placed immediately proximal to the ankle joint of the involved limb and fastened firmly around the chair’s leg. A force gauge will be secured between the medial side of the leg and the stabilization strap. The participant will be instructed to pull his/her leg inward with maximal effort until the force value is displayed on the force gauge. The test will be repeated 3 times at a 20-second interval. The mean value will be recorded [45]. The maximum isometric hip external rotation test was reported reliable in healthy subjects (SE 3.9, ICC 0.88) [45].

##### Maximum Isometric Trunk Rotation Force

The participant will be positioned on the chair in the sitting position with feet resting on the floor. Two nonelastic belts will pass diagonally over the chest and shoulder and finally are wrapped and secured around the back of the chair. Another belt will be fastened on the thighs to prevent extraneous pelvic movement. The force gauge will be fixed between the subclavicular area and the diagonal strap at one side. The participant will be asked to rotate his/her trunk toward the opposite side and exert isometric force to the force-probe, held in this position for 5 seconds. The test will be repeated thrice at a 20-second interval. The mean value will be recorded. The test will be performed on the opposite side using the same procedure [46]. A portable dynamometer provides suitable reliability and validity values to test different trunk muscles and populations [47]. Adequate reliability for the measurement of trunk rotator muscles was presented in subjects with stroke (ICC 0.64-0.99, SEM was considered low) [46] and older adults (ICC≥0.75) [48].

#### JPR of Hip Abduction

Hip proprioception will be measured using the active JPR while standing. The participant will stand with closed eyes on the uninvolved leg on a 10-cm-high wooden block. The involved leg will be allowed to freely move and abduct the hip joint. The participant will maintain his/her balance throughout the tests by touching a horizontal bar at hip joint height. During the first trial, the examiner will sit behind the participant and check the reference position and target angle. The hip abduction angle will be quantified using a large protractor attached in front of the participant on the wall. The protractor and hip joint center (greater trochanter) will be matched before starting the trial. The reference position is when the tested leg is placed parallel to the supporting limb in which the medial side of the tested leg is adjusted on the zero degrees of the protractor. The participant will randomly select the target angle within 10° to 40° for 4 trials. Three reflective markers will be attached to the apex of the iliac crest, greater trochanter, and lateral femur epicondyle [49]. The movement of the reflective markers will be recorded using a Canon camera (EOS-500D, DS126231) placed behind the participant at a distance of 2.5 m. The participant will be asked to actively move his/her leg from the reference position to the selected target angle at their self-selected velocity.

In the first trial, the examiner will instruct the participant on the “STOP” command to inform him/her of reaching the target angle. The participant will hold their leg at the target angle for approximately 4 seconds to memorize it. Then, the examiner will ask the participant to return his/her leg to a reference position of 0° by saying “Return” and holding the leg there for 3 seconds. Next, the participant will be asked to actively reproduce the previous target angle 3 times [49]. The camera’s tracking angles will be analyzed using Kinovea software (Version 0.9.2). Kinovea software is a valid and reliable tool to measure angle and distance accurately [50]. Intrasession reliability for angular error in hip abduction movement in healthy adults was reported between 0.39° and 0.96°, indicating a lower measurement error or more precise score for the hip joint proprioception test [49].

#### Demographic and Clinical Data

Demographic and clinical characteristics, including age, weight, height, BMI, duration of symptoms, and involved limb, will be prospectively collected and recorded on report forms.

### Data Analysis

All data will be saved with identification codes to maintain confidentiality. Every effort will be made to follow up on all subjects by the examiner. All enrolled participants, including those who do not complete treatment, will be included in the analysis on the basis of the intention-to-treat principle. Missing data will be replaced by the mean imputation technique, in which the mean of the observed values will be calculated and reported. Descriptive statistics will present demographic characteristics and outcome measures for each intervention group. Multivariate ANOVA will be used to test between- and within-group differences. Data will be controlled for outliers and checked for the normality and homogeneity assumptions. Post hoc (Bonferroni) tests will be conducted to report pair-wise comparisons. SPSS (version 17.0; SPSS, Inc) will be used for statistical analysis, and statistical significance will be set at a *P* value of <.05.

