### Sample Size

In total, 84 women with postpartum PPGP will be recruited. The optimal sample size was calculated on the basis of the results of a previous study [32]. The pain intensity for intervention groups was 58.2 (SD 13.93) and 64.4 (SD 13.96) at baseline, respectively [32]. We estimated a sample size of 25 in each study arm, which would yield 60% power (α=.1) and an effect size of 0.44 (Cohen *d*) in accordance with calculations performed using G*power software (Version 3.1, Universität Düsseldorf). We also considered an overall dropout rate of 10% (eg, lost to follow-up). Therefore, we aimed to recruit 84 participants (28 in each study arm).

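### The plan fixes single mean imputation for the intention-to-treat analysis without saying which mean: at 10% dropout the standard error is about 11% too small, or the difference is diluted by up to about 11%, depending on the reading

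*Protocol article*

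**What the plan says.** The rule is in the protocol article, Methods, Data Analysis: "Missing data will be replaced by the mean imputation technique, in which the mean of the observed values will be calculated and reported". The same section defines who is analysed: "All enrolled participants, including those who do not complete treatment, will be included in the analysis on the basis of the intention-to-treat principle". Filled-in values therefore enter the main analysis. That analysis is given as "Multivariate ANOVA will be used to test between- and within-group differences", followed by Bonferroni pairwise comparisons, and "statistical significance will be set at a *P* value of <.05".

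The Sample Size section shows that missing data are expected: "We also considered an overall dropout rate of 10% (eg, lost to follow-up". It raises 25 per arm to 28: "Therefore, we aimed to recruit 84 participants (28 in each study arm". Table 1 schedules pain at four time points (T1 to T4) and the disability index at three (T1, T3, T4). These are the two primary outcomes.

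The article does not say over what the mean is taken. It gives no variance correction to accompany the imputation.

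**The concern.** Single mean imputation puts a constant in place of an unknown value and then counts it as data. The consequence depends on which mean is used.

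- **Arm mean:** the imputed values add nothing to the within-arm sum of squares but raise the sample size, so the standard error is too small and false positives rise.
- **Overall mean:** every arm is pulled towards the others, so the treatment difference shrinks.
- **Participant's own mean over visits:** T1, taken before any treatment, is averaged into a T3 or T4 value, so an effect that appears after baseline is diluted.

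The arm and overall means also ignore what is already known about the participant from her other visits. The rule applies to both primary outcomes. Leaving the choice of mean open also allows it to be made after the data are seen. This is a stated rule, not a detail left to a separate analysis plan.

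**Working it through.** **Inputs.** Recruited per arm N = 28; planned dropout 10%; standardised effect 0.44; analysis level 0.05 (all from Sample Size and Data Analysis). Assumed: equal numbers missing per arm, completely at random, one outcome at one visit.

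**The plan's own figures.** Sample Size reports "The pain intensity for intervention groups was 58.2 (SD 13.93) and 64.4 (SD 13.96) at baseline, respectively". The difference is 64.4 − 58.2 = 6.2, the average SD is 13.945, and 6.2 / 13.945 = 0.445, matching the stated 0.44. With 10% dropout, 25 / 0.9 = 27.8, rounded up to 28, and 3 × 28 = 84. Both reproduce. (The 25 per arm at 60% power reproduces only with a one-sided α of 0.1. That is a separate matter and is not used here.) The expected loss is 28 − 25 = 3 per arm, or 10.7%. So r = 25 are observed.

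**Arm mean.**
- Reported SE / true SE = √[(r−1)/(N−1)] × √(r/N) = √[(24/27) × (25/28)] = √0.794 = 0.891, so the SE is about 11% too small.
- Implied two-sided type I error = 2 × [1 − Φ(1.96 × 0.891)] = 0.081.
- Simulation (three arms, SD 13.945, 40,000 runs): reported SE 3.50 against 3.93 for the observed data; type I error 8.0% for an unadjusted pairwise test and 9.0% for the three-arm overall test; coverage of the 95% interval about 92%. At the Bonferroni level of 0.05 / 3 = 1.67%, a two-arm simulation gives 3.4%.
- The estimate itself is unbiased (6.19 for a true 6.2).

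**Overall mean.**
- With equal missingness the difference is multiplied by r/N = 25/28 = 0.893: 0.44 becomes 0.39, and 6.2 becomes 5.54.
- Simulation: type I error 4.9–5.0%, coverage about 95%. Power for the pairwise test is about 34%, the same as for the observed data alone.

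**Participant's own mean.** Assume only T4 is missing and the effect is constant at 0.44 from T2 onwards.
- The imputed value carries an effect of (0 + 0.44 + 0.44)/3 = 0.293.
- Expected difference = (25 × 0.44 + 3 × 0.293)/28 = 0.424.
- Simulation with within-person correlation 0.5 to 0.7: estimate about 0.425, type I error about 5%, coverage 95%.
- If T3 and T4 are both missing, the imputed effect is (0 + 0.44)/2 = 0.22 and the T4 difference is (25 × 0.44 + 3 × 0.22)/28 = 0.416. If only T1 was observed, the imputed effect is 0 and the result is 0.393, the same dilution as under the overall mean.

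**Reference.** Analysing the observed values only, with 3 of 28 missing: overall type I error 4.9%, estimate 6.21, reported SE 3.93 against an empirical 3.94, coverage 95.0%.

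**Range.** Missingness other than 10% is an assumption, not a figure from the protocol.

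| Missing per arm | Arm mean: SE ratio | Arm mean: pairwise type I error | Arm mean: three-arm overall type I error | Overall mean: difference (true 6.2) |
|---|---|---|---|---|
| 1 of 28 (3.6%) | 0.96 | 6.0% | 6.1% | 5.98 |
| 3 of 28 (10.7%) | 0.89 | 8.0% | 9.0% | 5.54 |
| 6 of 28 (21%) | 0.78 | 12.6% | 15.8% | 4.87 |
| 8 of 28 (29%) | 0.71 | 16.4% | 21.8% | 4.43 |

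**The case against.** The strongest reply is that the harm depends on a reading the text does not settle. Error inflation occurs only with the arm mean. Under the overall mean, type I error and power match an analysis of the observed data, and an 11% attenuation (0.66 points when the true difference is 6.2) is small beside a standard error near 3.5. Under the participant's own mean, almost nothing happens if only T4 is missed. All of this stands, and it limits the size of the point.

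Some stronger conclusions are tempting and are not supported:

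- A reader might infer that the results will be wrong under every reading, or that every reading discards the participant's own earlier values. The own-mean reading uses them, and its error rate stays near 5%.
- A reader might infer that the error inflation and the dilution add up. They belong to different readings.
- A reader might infer that earlier pain scores make pain-related dropout harmless once they are used. That holds only if dropout depends on recorded values; dropout driven by unrecorded pain is not covered.
- A reader might infer a known distortion of the multivariate test. The calculations cover one outcome at one visit; the planned multivariate analysis was not simulated.

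What the reply does not do is rescue the rule. No reading represents the uncertainty in the filled-in values, none is better than the alternatives available from the same data, and the protocol does not say which is meant.

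**Conclusion.** The sentence is wrong as written and should be replaced before analysis. At the plan's own dropout rate the damage is moderate: about 8% type I error for a nominal 5% and about 92% coverage if the arm mean is used; 0.44 reduced to 0.39 if the overall mean is used; about 0.425 if the participant's own mean is used and only T4 is missing. The alternatives cannot be narrowed further, because the article does not specify the mean. The figures rest on equal missingness, completely at random, in one outcome at one visit. The own-mean figure also assumes a constant effect after baseline and a within-person correlation near 0.6. Higher missingness makes the distortions larger, but the protocol does not predict it.

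**What to change.** Strike the mean-imputation sentence and put one of these in its place:

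1. Analyse all observed visits of all randomised participants in a likelihood-based repeated-measures model with arm by visit and the baseline value as covariate. No imputation is needed.
2. Keep the planned analysis, but precede it with multiple imputation by arm from the participant's other visits, and combine the results so that the imputation uncertainty reaches the standard errors.

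Both are valid under missing at random. Align the sentences on the multivariate ANOVA and the Bonferroni comparisons with the choice made; under option 1 they have to be rewritten, not just supplemented.

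Any sensitivity analysis for data not missing at random should shift the missing values separately by arm. A common shift in both support arms largely cancels in lumbar versus pelvic support, which is the article's second aim, and would test only each support against control.

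The cost is a few sentences, a little more analysis work, and slightly wider confidence intervals than arm-mean imputation would report. For observed data alone the SE is 3.93 against 3.50, a factor of 1.12, and that width is the correct one. No extra participants, visits or measurements are needed.
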